### 2.8. Statistical Analysis

Quantitative data will be analyzed using SPSS Statistics 22.00 for Windows. Parametric statistical tests will be employed with a significance level set at *p* < 0.05. To compare outcome variables between interventions, the paired Student’s *t*-test will be employed for comparisons involving two measures. For comparisons involving more than two measures, repeated measures ANOVA will be used to identify specific differences between groups or time points. To provide a comprehensive understanding of the results, effect sizes will be calculated for both the *t*-test and ANOVA. Confidence intervals for these effect sizes will also be reported to offer insights into the robustness of the findings.

Photovoice data will be transcribed by the researchers who conducted the online meetings with the families. The transcriptions will be reviewed by an experienced qualitative researcher [48]. Two researchers will independently analyze the data, followed by a group discussion with the research team to develop preliminary results. Thematic analysis will be performed following the principles outlined by Braun and Clarke [49] with support from ATLAS.ti software v.23. Identified themes will be validated by the participating families, who act as co-investigators in this study. This phase, termed “Validation of Analysis by Parents”, allows families to select the themes that best reflect the content of the sentences and photos included in the analysis.

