## Abstract

**Background**: Young children with spinal muscular atrophy type 1 (SMA1) have limited independent mobility and participation that may lead to cognitive development delays. Implementing early powered mobility in interventions may help them to learn self-initiated movement, play, and having fun to participate in natural settings. The aim of this study is to evaluate the effectiveness of an early power mobility intervention for increasing participation, functional ability, and quality of life in young children with SMA1. **Methods**: AMEsobreRuedas is a randomized waiting list controlled clinical trial. A sample of 24 children (10 months-5 years old, with SMA1) will be randomly allocated to two groups. The experimental group will perform a family-centered intervention with powered mobility for 16 weeks in their natural environment: a 12-week-structured program three times a week; and a 4-week follow-up with free use of the powered mobility device. The control group (waiting list) will keep their routine and will receive the same intervention after the experimental group. Five assessments will be carried out at baseline and weeks 4, 8, 12, and 16. Primary outcomes are participation (YC-PEM); functional ability (PEDI-CAT); and quality of life (PedsQL-Neuromuscular module). **Results**: It is expected that this study will provide further knowledge about the positive impact of powered mobility for the analyzed variables. Moreover, family engagement in the intervention and establishment of functional goals may help to add valuable information about real needs in future research. **Conclusions**: Early powered mobility could increase the opportunities for children with SMA1 to learn to move independently and participate in their natural environment.

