### 2.1. Study Sample

Children with SMA1, between 10 months and 5 years old, who have no prior experience with powered mobility interventions or have used a powered mobility device for less than 7 h in the month preceding this study will be included. Exclusion criteria are children with severe visual impairments, a body weight exceeding 25 kg—MROC requirement, those who use a respirator, or those with other health conditions affecting the neuromusculoskeletal system that may interfere with the use of powered mobility [26,29].

Sample size calculation was performed using G*Power version 3.1.9.4. The calculation was based on the following parameters: an alpha (α) level of 0.05, which corresponds to a 5% chance of a type I error (incorrectly rejecting the null hypothesis when it is true); a statistical power (1-β) of 0.80, which means there is an 80% chance of correctly rejecting the null hypothesis if there is a true effect; and a medium effect size of 0.5 due to the lack of previous studies in this population and the use of powered mobility. Based on these parameters, the calculation determined that 26 participants, with 13 participants in each group, would be needed to achieve adequate statistical power for this study. To account for a potential dropout rate of 20%, a total of 32 participants will be recruited (*n* = 16 for each group) to ensure that the final sample size remains sufficient for analysis.

Recruitment will be performed at early care centers in collaboration with the Spanish Spinal Muscular Atrophy Foundation (*FUNDAME: Fundación de Atrofia Muscular Espinal*). An informational session will be held with the families of potential participants to explain the aims and procedures of this study.

Once families have shown their desire to participate and signed the informed consent forms, a member of the research team—not involved with assessments or interventions—will randomly assign the participants to two groups: the experimental group and the control group (waiting list group).

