### 2.2. Outcome Variables

Outcome variables will be measured by a blind evaluator, member of the research team. Data will be collected at baseline, during intermediate assessments at weeks 4, 8, and 12 throughout the structured program, and at a follow-up assessment at week 16, depending on each specific variable, described as follows.
*Primary outcomes:* measured at baseline, at weeks 8 and 12—during and after the structured intervention—and at week 16 after the follow-up period.

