
### 2.3. Study Flow

This study will last 16 weeks. Participants in the experimental group will undergo a structured powered mobility intervention, consisting of 30 min sessions conducted three times a week for 12 weeks. Following this, there will be a 4-week follow-up period during which children in the experimental group have unrestricted use of the powered mobility device. In contrast, participants of the control group will continue with their usual routines during the intervention period. After the 12-week intervention phase, the control group (waiting list) will receive the same powered mobility intervention as the experimental group. Figure 1 illustrates the *AMEsobreRuedas* study flowchart.

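### Section 2.8 names a paired t-test to compare the interventions, but the arms are unmatched randomised children; the ANOVA sentence beside it does not fix the between-arm contrast either

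*Protocol article*

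**What the plan says.** Section 2.8 of the protocol article gives two rules for the quantitative outcomes.

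- Two measures: "To compare outcome variables between interventions, the paired Student’s *t*-test will be employed for comparisons involving two measures".
- More than two measures: "For comparisons involving more than two measures, repeated measures ANOVA will be used to identify specific differences between groups or time points".

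The design to which these rules apply is set out elsewhere in the article.

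- Section 2.1 (Study Sample) has a member of the team "randomly assign the participants to two groups: the experimental group and the control group (waiting list group"). No matching of children is described.
- Section 2.2 (Outcome Variables) has the primary outcomes "measured at baseline, at weeks 8 and 12—during and after the structured intervention—and at week 16 after the follow-up period", which makes four assessments.
- Section 2.3 (Study Flow) adds: "After the 12-week intervention phase, the control group (waiting list) will receive the same powered mobility intervention as the experimental group".

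The threshold is a "significance level set at *p* < 0.05". Sidedness is not stated.

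**The concern.** A paired t-test works on differences between linked observations. Two arms of unmatched children have no such links. The sentence that says how interventions will be compared therefore names a test that does not fit the comparison. It can be carried out in only two ways:

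1. **Within children**, for example baseline against week 12 in one arm. This is a valid test of change, but not of the intervention against waiting.
2. **Across arms**, by pairing each experimental child with an arbitrary control child. The result then depends on the arbitrary pairing, and the test is undefined if dropout leaves unequal arms.

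The first is the harmful one. The children are 10 months to 5 years old. The Introduction notes that disease-modifying therapies are improving function in SMA1. All three primary outcomes are parent- or family-reported, and families run two of the three weekly sessions (Section 2.6). Scores could move over 12 weeks without any effect of the device. Since the stated aim is to show effectiveness, the test that carries that claim has to be a contrast between the randomised arms.

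**Working it through.** **Step 1. Which outcomes fall under which rule.** Counting assessments in Section 2.2:

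| Outcome | Assessments |
|---|---|
| YC-PEM, PEDI-CAT, PedsQL (primary) | 4 each |
| GAS | 5 |
| PSI-SF | 4 |
| CSQ-8 | 3 |
| ALP | weekly |
| QUEST 2.0 | 1 |

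No outcome has exactly two assessments. By count, the primary outcomes go to the ANOVA. The paired rule applies when someone picks out two values, such as baseline and week 12, or the two arms at one visit. The plan does not say which it means.

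**Step 2. Can the waiting-list design supply genuine pairs?** Only control children have both an untreated and a treated period. Pairing those periods is a valid within-child comparison, but it is not randomised and is confounded with time and growth.

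**Step 3. Does the ANOVA sentence settle the between-arm test?** It can compare arms. But its wording (groups or time points) is also satisfied by a main effect of time, which says nothing about the intervention. The group-by-time term is not named. Using all four assessments also brings in week 16, when on the wording of Section 2.3 controls are no longer untreated.

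**Step 4. Size of the within-arm problem.** Inputs from the article: "an alpha (α) level of 0.05" and 13 children per arm (Section 2.1). Assumptions: two-sided test, no intervention effect, a common change of δ SD in both arms, pre-post correlation ρ. The article gives neither δ nor ρ.

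- SD of the change = √(2(1 − ρ)); standardised change dz = δ / √(2(1 − ρ)); noncentrality = dz·√13; df = 12; critical t = 2.179.
- δ = 0.3, ρ = 0.5: SD 1.000, dz 0.300, noncentrality 1.082, rejection 16.9%.
- δ = 0.3, ρ = 0.8: SD 0.632, dz 0.474, noncentrality 1.710, rejection 35.0%.

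| Common change | ρ = 0.5 | ρ = 0.7 | ρ = 0.8 |
|---|---|---|---|
| 0 | 5% | 5% | 5% |
| 0.3 SD | 17% | 25% | 35% |
| 0.5 SD | 38% | 57% | 74% |

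A simulation (40,000 runs, ρ = 0.5) gives 5.1%, 16.8% and 38.0% for the three rows. An independent t-test on change scores in the same runs stays at 4.8% to 5.0%.

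**Step 5. Size of the arbitrary-pairing problem.** With 13 per arm, df fall from 2·13 − 2 = 24 to 13 − 1 = 12. The noncentrality is unchanged at d·√(13/2).

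- At d = 0.5 it is 1.275; power is 23.2% for the independent test and 21.7% for the paired one.
- At d = 1.0 it is 2.550; power is 68.7% and 64.9%.

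Simulated type I error under arbitrary pairing stays at about 5%.

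**The case against.** The best defence is that the paired sentence should not be read alone. The sentence after it names a repeated measures ANOVA that can compare groups, all three primary outcomes have four assessments, and no listed outcome has exactly two. On that reading the primary comparison goes to the ANOVA, and the paired test serves pairwise contrasts within children or the waiting-list children's own before-and-after comparison. This largely stands, and it limits the reach of the point.

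A reader might infer that the plan discards the control group, or that it will judge effectiveness by significance in one arm and not in the other. The document does not support either. It provides for a group comparison and nowhere says that within-arm tests will carry the effectiveness claim.

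It is also fair that the rejection rates rest on assumed drift. SMA1 is a progressive disease, a positive common change cannot be presumed, and with none the rate is 5%.

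What the defence does not remove is the wording. The sentence assigns comparisons between interventions to a paired test, which is wrong for these arms whatever a fuller analysis plan may add. Nor does the ANOVA sentence, as written, say which term answers the trial's question.

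**Conclusion.** The point holds in limited form. The paired t-test is the wrong test for any comparison between the arms, and the control children's later treatment does not rescue it. A between-arm analysis of the primary outcomes is available through the ANOVA, but the text does not tie the effect to the group-by-time term or stop it before controls start the intervention.

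The size is conditional. If within-arm paired tests were used to claim effectiveness, the false-positive rate at 13 children would be 17% to 35% for a common change of 0.3 SD, and 5% for none. Those figures rest on an assumed drift, assumed correlations of 0.5 to 0.8 and a two-sided test. Arbitrary pairing is minor by comparison: about 1.5 percentage points of power at d = 0.5 (23.2% − 21.7%), with type I error near 5%.

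The week-16 remark relies on Section 2.3. The Abstract says only that controls are treated after the experimental group, and the flowchart is not shown.

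**What to change.** Replace the paired t-test for comparisons between arms with an independent-groups analysis, and state one primary contrast for each primary outcome:

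- Time point: week 12, before controls start the intervention.
- Method: ANCOVA of the week-12 score on randomised group, adjusted for the baseline score. An acceptable alternative is the group-by-time term of the repeated measures ANOVA already planned, restricted to assessments up to week 12.
- Report the mean difference between arms (adjusted, under ANCOVA) with its 95% CI.
- Keep paired t-tests for descriptive within-arm change, including the control children's waiting and treated periods, and state that they do not support a claim of effectiveness.

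The cost is one paragraph of wording. The week-12 and baseline scores are already scheduled, so no new data are needed.

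### The estimates that Section 2.8 commits to, effect sizes for a repeated measures ANOVA and a paired t-test, do not as stated give the size or direction of the between-arm effect

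*Protocol article*

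**What the plan says.** Section 2.2 says that the primary outcomes (YC-PEM, PEDI-CAT and the PedsQL neuromuscular module) are "measured at baseline, at weeks 8 and 12—during and after the structured intervention—and at week 16 after the follow-up period". That is four visits.

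Section 2.8 sets the analysis by number of measures. The paired Student's "test will be employed for comparisons involving two measures" is one branch. The other reads: "For comparisons involving more than two measures, repeated measures ANOVA will be used to identify specific differences between groups or time points".

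On estimation, Section 2.8 says that "effect sizes will be calculated for both the" t-test and the ANOVA, and then: "Confidence intervals for these effect sizes will also be reported to offer insights into the robustness of the findings". It does not name the effect-size index. It mentions no between-arm mean difference in scale points and no interval for one. It also does not say that arm means will be left out.

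Section 2.3 keeps controls on their usual routine during the intervention period and gives them the intervention after the 12-week phase.

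**The concern.** The aim in the Introduction and Discussion is effectiveness, and the design compares the intervention with a waiting list. The quantity that answers this is a signed difference between arms on each instrument, with its uncertainty.

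Neither stated estimate is that quantity. An omnibus ANOVA effect size of the usual kind describes how much variation an effect accounts for. It does not say which arm did better or by how many points, and its interval has a lower limit of zero, so it cannot point to harm. The effect size of a paired t-test has a sign, but it describes change within children. Participants are 10 months to 5 years old, so some change over 12 to 16 weeks is plausible without any intervention.

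If these were the main reported estimates, a reader would have intervals around quantities that do not answer the trial's question.

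**Working it through.** **Inputs**
- Groups: 2 (Section 2.1).
- Visits for primary outcomes: 4 (Section 2.2), or 3 if analysis stops at week 12.
- Children: 26 analysable, 13 per group, and 32 recruited (Section 2.1); 24 (Abstract).
- Index: not stated. Partial eta squared is assumed in steps 3 and 5.

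**1. The plan's own figure.** The plan gives no expected ANOVA effect size. Its nearest figure is the planning effect of 0.5 that led to 26 children, and Section 2.1 does not say whether this is d or f. A repeated measures ANOVA (between factors) with f = 0.5, two groups, two measures and correlation 0.5 has noncentrality f²Nm/[1 + (m − 1)ρ] = 0.25 × 26 × 2/1.5 = 8.67. For it, 26 is the smallest even total that reaches 80% power. A two-sided two-sample t-test with d = 0.5 needs 64 per arm. So 26 can be reproduced, but only with options the article does not state.

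**2. Which rule applies.** Four visits are more than two measures, and so are three. Either way each primary series goes to repeated measures ANOVA.

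**3. Partial eta squared with no effect.** With normal errors and sphericity, partial eta squared follows a Beta(df1/2, df2/2) distribution under the null, with mean df1/(df1 + df2).
- Group effect: 1/(1 + N − 2) = 1/(N − 1).
- Group-by-time with m visits: (m − 1)/[(m − 1) + (N − 2)(m − 1)] = 1/(N − 1).
- N = 26: 1/25 = 0.040 (check: 3/75 with four visits, 2/50 with three).
- N = 24: 1/23 = 0.043.
- N = 32: 1/31 = 0.032.

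A simulation of the group-by-time effect (20,000 trials, N = 26, four visits, assumed correlation 0.5) gave mean 0.040, median 0.033 and a central 95% range of 0.003 to 0.121.

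**4. Other indices, same null simulation, N = 26.** Cohen's f averages about 0.19 and omega squared about 0.00. Omega squared removes the upward bias and can fall below zero. A negative value only means that F is below 1; it does not indicate harm.

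**5. Direction.** The same simulation was run with the experimental arm moving steadily to +0.5 SD, or to −0.5 SD, by the last visit. Mean partial eta squared was 0.062 in both cases, so equal benefit and equal harm look the same on this index.

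**6. Paired effect size.** With equal SDs at the two visits, mean change over SD of change is δ/√[2(1 − r)], where δ is change in SD units and r the between-visit correlation. For maturation of 0.2 SD and r = 0.8 (both assumed; the article gives neither), this is 0.2/√0.4 = 0.32 with no treatment effect.

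**The case against.** **This is a condensed article, so the estimate may be in the full plan.** This has weight. Silence on the index, or on tables of means, would not be a finding by itself. But Section 2.8 is not silent on estimation: it says which estimates will carry confidence intervals. The point concerns that stated choice.

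**Section 2.8 does not withhold direction.** A reader might infer that the results could not show how much, or which way, children changed. The text does not support that. The ANOVA is meant to find specific differences between groups or time points, which implies follow-up comparisons that would have a sign. Arm means are routine output, and a paired effect size shows the direction of change within children. What stands is narrower: no signed between-arm estimate with an interval is committed to.

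**The figure of 0.04 is not fixed by the plan.** Correct. It holds for partial eta squared at N = 26. The value is 0.032 or 0.043 at the other stated sample sizes, and about zero for omega squared.

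**A null result would not pass unnoticed.** Also fair. Section 2.8 plans significance tests, and a non-significant F would come with an interval reaching zero.

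**Comparison with the planned 0.5.** A reader might set the null value against the planning effect and conclude that a trial with no effect would look close to plan. That fails because the index is unstated. If 0.5 is d, then f = 0.25 and eta squared = 0.0625/1.0625 = 0.059. If 0.5 is f, eta squared = 0.25/1.25 = 0.20. No such comparison is relied on here.

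**Conclusion.** The point holds in limited form. All three primary outcomes fall under the ANOVA rule, and the only estimates with intervals that Section 2.8 states are effect sizes for that ANOVA and for a paired t-test. Neither, as stated, is an estimate of the between-arm effect.

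The absence of sign and units applies to eta squared, partial eta squared and f. The upward bias, a mean of about 0.03 to 0.04 with no effect, applies to partial eta squared, assuming normal errors, sphericity and 24 to 32 children. The maturation example rests on assumed values and only shows the mechanism.

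This is a weakness in how the result would be expressed. It does not show that the trial would hide a null or harmful result, and it does not affect the data collected. It is worth correcting before analysis because the better estimate is available from the same visits.

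**What to change.** In Section 2.8, name as the estimate for each primary score the baseline-adjusted between-arm difference in instrument points at week 12, with its 95% confidence interval. Under Section 2.3, week 12 is the last visit before controls start the intervention. The repeated measures ANOVA can stay as a supporting analysis.

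If a standardised value is also wanted, name a signed between-arm index, for example that difference divided by the pooled baseline SD with the Hedges small-sample correction. State that omnibus ANOVA and paired effect sizes are descriptive and will not serve as the evidence of effectiveness.

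The cost is analysis wording only. Baseline and week 12 are already planned for every primary outcome, so no visit, instrument or participant is added.

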## 3. Results

This randomized controlled trial (RCT) aims to enhance understanding of the positive impacts of powered mobility on participation, functional ability, and quality of life in children with SMA1. It is anticipated that this intervention will lead to a significant improvement in these areas.

Specifically, it is expected that children will demonstrate an increase of at least 2 points in their ALP level during the structured program. Furthermore, ongoing progress is anticipated throughout the follow-up period, reflecting sustained benefits from the intervention.

Family involvement in the implementation of the intervention and the establishment of functional goals is crucial. Engaging families not only facilitates the practical application of the intervention but also provides valuable insights into the real needs and challenges faced by children with SMA1. This feedback will be instrumental in refining future research and therapeutic strategies.

By exploring these factors, this study aims to offer more precise guidance on optimizing therapeutic approaches for this vulnerable population. The results will provide a more comprehensive overview of the study’s goals and anticipated outcomes, emphasizing the importance of family involvement and the potential impact on future research and therapeutic strategies.

